**Fig. 1 Fig1:**
[figure not shown]
Study flow chart

The primary outcome is the incidence rate of the recurrence of fistula. For the purpose of this study, recurrence of fistula includes the breakdown of a repaired fistula or the occurrence of a new fistula in study participants. At the study sites, the closure of fistula was determined at hospital discharge by a pelvic exam using a dye test. During follow-up visits, women will first be asked about current medical status using the question “does the woman have continuous and uncontrolled leakage of urine?”. If the answer is “YES” then women will be scheduled for a pelvic exam with a dye test for confirmation, at the nearest health facility (health centre or health post). This question is always used at EngenderHealth supported sites to assess women at reception, before further pelvic exam. In addition, the presence of “continuous and uncontrolled leakage of urine” is commonly used as a screening question for fistula in circumstances in which a pelvic exam is not possible (e.g. Demographic and Helath Surveys, DHS); it differentiates between fistula and other forms of incontinence, which are unlikely to be continuous and uncontrolled. In some cases, it might not be feasible to perform the dye test if for instance the woman refuses to go to a health facility. This might lead to a misclassification which can bias the estimate towards a null. However, misclassification is unlikely, since women with continued urinary leakage are eager to report their experiences in order for the condition to be rectified.

The secondary outcomes include pregnancy and pregnancy and outcomes (miscarriage or abortion or term pregnancy). Pregnancy and pregnancy outcomes will be documented by a positive pregnancy test from discharge (done at recruitment or during follow-up visit or given at any time by a result from medical records such as antenatal (ANC) card) or by a self-reporting corroborated by 2 witnesses. Maternal status at delivery and mode of delivery (dead or alive; caesarean section or normal delivery; no complication or any complication) will be assessed by looking at the ANC & Delivery card or hospital records or self-reporting. Child outcome at delivery (stillbirth, neonatal death or alive) will be assessed by looking at the ANC & Delivery card or hospital records or self-reporting corroborated by 2 witnesses.

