### Study setting

#### General setting

Guinea is a coastal West African country with an estimated population of 12 million people [6]. The population is largely rural (65 %) and poor [30]. The Guinean health care system faces many challenges, including chronic shortage of qualified physicians and nurses, and poor clinical infrastructure, particularly in rural and mountainous areas. According to the national action plan for repositioning family planning in Guinea 2014–2018 [20], only 16 % of health professionals (doctors, state midwives and state nurses) work in rural areas where they serve 65 % of the population. Guinea has an estimated lifetime prevalence of obstetric fistula of 0.6 % among women aged 15–49 which ranges regionally from 0.2 to 1.2 % [6], although this figure is likely underestimated. Challenging contextual factors in maternal health include low modern contraceptive prevalence (6 %), concurrent high fertility rate of 5.1, and high maternal mortality (724 deaths per 100,000 live births) [6]. Over the period 2007–2012, the majority of births (54.7 %) were assisted by untrained individuals, and occurred at home (58.8 %) [6]. Since 2012, the Ministry of Health has elaborated a national strategic plan (2012–2016) for the prevention and treatment of fistula [16]. This strategic plan emphasizes the importance of reintegration and support to victims of OF and advocates for more operational and action research that can inform policy.

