### Participants’ recruitment and follow-up

All women who underwent successful repair of OF from January 1, 2012 to June 30, 2015 at the 3 study sites are eligible for inclusion in study. However, only women with a unique obstetric fistula that was closed at discharge, as measured by a dye test, who provide written informed consent, reside in Guinea and agree with follow-up visits will be included in the study (Fig. 1). Eligible participants who refuse informed consent, who got repair outside the study sites or whose medical records are incomplete will be excluded.

Individual medical records of all women who benefited fistula repair at the 3 sites in 2012–2015 will be screened by the study team to identify those who were discharged with a close fistula (Fig. 1). After locating them through their medical records, the study team (that includes nurses called “Fistula Counsellors” who are involved in the management of women at the fistula repair sites) will contact women by home visit in their community to obtain informed consent.

Once the informed consent is obtained, the woman will be interviewed for 30 − 60 min by the study team and examined in an isolated place for inclusion in the study. Later, her medical records will be used at the fistula repair site where she got the surgery to collect her sociodemographic and clinical characteristics at the time of surgery. For all women recruited in the study, most retrospectively, new fistula or recurrence of the repaired fistula, pregnancies and their outcomes (miscarriage, stillbirth, live birth, early new-born death, maternal death, and type of maternal complication) will be documented. Health Centres and Health posts around which the study participants live will be used by the study team to perform the dye test in women who report “Continuous and uncontrolled leaking” since discharge or at the follow up visit.

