**Fig. 2 Fig2:**
[figure not shown]
Study timeline

A home visit will then be conducted within the community to seek informed consent with the repaired women. After obtaining the consent, women will be interviewed. Women who report “Continuous and uncontrolled leaking” since the last follow-up visit will be scheduled for a pelvic exam and a dye test at the nearest health centre or health post. If the case is confirmed as fistula (by a dye test of clinical exam), the woman will be counselled and referred to the nearest fistula repair centre. By this approach, we think that any misclassification of outcome (recurrence of fistula) will be minimal, since women with any continuous and uncontrolled leakage of urine following repair are likely to report it, and any reported incontinence will be evaluated by a dye test.

If a woman reports pregnancy, she will be asked to show her antenatal care (ANC) & delivery card on which pregnancy test result is routinely reported. If possible, a pregnancy test will be performed. Otherwise, investigators will rely on woman self-reporting.

Sociodemographic and clinical characteristics of women will be collected from individual medical records at each participating fistula repair site.

All investigators will receive appropriate training at the Maferinyah National Research and Training Centre before they go in the field.

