### Data analysis

Categorical data and treatment outcomes will be summarized as frequencies (%) and compared using *χ*2 or Fisher’s exact tests as appropriate. Continuous data will be presented using median (interquartile range) and compared using the Wilcoxon rank-sum test. Follow-up will be calculated from the date of hospital discharge. The date of fistula recurrence or the estimated date of pregnancy will be selected as the date of events. Patients who do not experience recurrence of fistula or pregnancy will be censored at the last follow up visit. For patients who are reported dead (by the relatives), the date of death will be used to determine their follow-up time in the study. For patients who are lost to follow up (i.e. who move from their village without any address to joint them after inclusion) the date of the last visit will be used.

Socio-demographic and clinical differences between those women who remain in the study and those who are lost-to-follow-up will be estimated to check for any imbalances at inclusion.

The incidence of fistula recurrence and that of pregnancy will be estimated using the method of cumulative incidence. The cumulative incidence rate will be compared across risk factors using Kaplan-Meier methods. Exposure variables with a *P*-value <0.2 in the univariate analysis will be included in multivariate models. Exposure variables with a *P*-value <0.2 in the univariate analysis will be included in multivariate models. A risk factor analysis will be performed using adjusted Cox regression. Associations will be reported as adjusted hazard ratios with 95 % CIs. Analysis will be done using STATA version 12 (STATA Corporation, College Station, TX, USA) with a level of significance will be set at *P* < 0.05.

For the outcomes of pregnancy (miscarriage or abortion, mother and child status at delivery), Pearson’s Chi square (*χ*2) will be used to compare proportions of these outcomes between potential exposure variables (age group, previous repair (Yes/No), fistula status at hospital discharge, use of antenatal care, delivery by caesarean section, etc.). Logistic regression analysis and models will be used and associations will be reported as risk ratios with a level of significance set at *P* = 0.05 and a 95 % confidence intervals.

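### Maternal complications may come from records or from uncorroborated self-report, and antenatal care and caesarean delivery influence which source exists, so those comparisons can carry a source artefact of unknown size and direction.

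*Protocol article*

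**What the plan says.** The outcome is defined in the Study design section, in the text on secondary outcomes. Maternal status there covers survival, mode of delivery and complications, and the source rule reads "no complication or any complication) will be assessed by looking at the ANC & Delivery card or hospital records or self-reporting". The three sources are listed as alternatives, with no order and no requirement that all women be assessed the same way. For the child's outcome the same section is stricter: "ANC & Delivery card or hospital records or self-reporting corroborated by 2 witnesses". The witness condition is absent for the mother.

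The section on recruitment and follow-up confirms that complications are collected: "early new-born death, maternal death, and type of maternal complication) will be documented".

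The Data analysis section introduces the comparison with "For the outcomes of pregnancy (miscarriage or abortion, mother and child status at delivery" and lists among the exposures "use of antenatal care, delivery by caesarean section, etc". Associations are to be reported as risk ratios, tested at the 0.05 level.

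The General setting section says that most births in Guinea in 2007–2012 "were assisted by untrained individuals, and occurred at home (58.8" %).

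A card-first order appears only in Study procedures, and only for confirming a pregnancy: "she will be asked to show her antenatal care (ANC) & delivery card on which pregnancy test result is routinely reported", then a pregnancy test where possible, and "Otherwise, investigators will rely on woman self-reporting".

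**The concern.** A comparison of complication risk between two groups is fair only if complications are detected about equally well in both. Here the way they are detected is tied to the exposure. A caesarean takes place in a hospital, which keeps a record. A woman who had no antenatal care has no antenatal record. A woman who delivered at home without antenatal care will usually have nothing but her own account, often given long after the event, since most women enter retrospectively.

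If records and self-report differ in accuracy, the misclassification is differential by exposure. Adding covariates to the logistic model does not remove it, and a larger sample does not shrink it. The article discusses misclassification only for fistula recurrence.

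At stake are the associations of antenatal care and caesarean delivery with maternal complications. They fall under the second study objective, which covers factors associated with maternal and perinatal pregnancy outcomes. Either exposure could look harmful or protective for the mother when only the data source differs.

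**Working it through.** The plan gives no figure on this point, so there is none to reproduce. The check asks how large an artefact the source rule could create when the exposure has no effect at all.

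**Input from the document.** Home births 58.8 % (General setting), so 1 − 0.588 = 0.412 is taken as one possible share of unexposed women with a record. This is a national share of all births, not a figure for this cohort or for non-caesarean births.

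**Assumed inputs, since the document gives none.** True complication risk 20–50 %, equal in both groups; sensitivity of records 0.7–0.9; sensitivity of self-report 0.5–0.9; specificity 0.95 for both sources, or 1 in the simpler version. All exposed women have a record. The share of unexposed women with a record, q, is 0.8, 0.412 or 0.

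**Formula.** Observed risk = true risk × [q × Se(record) + (1 − q) × Se(self)] + (1 − true risk) × (1 − Sp). The spurious risk ratio is the observed risk in the exposed (q = 1) divided by that in the unexposed.

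**Worked case.** True risk 0.30, Sp 0.95, Se(record) 0.9.

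- Exposed: 0.30 × 0.9 + 0.70 × 0.05 = 0.305.
- Unexposed, q = 0.412, Se(self) 0.7: 0.30 × (0.412 × 0.9 + 0.588 × 0.7) + 0.035 = 0.270. Ratio 0.305/0.270 = 1.13.

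**Other cases at true risk 0.30, Sp 0.95.**

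| Se(record) | Se(self) | q = 0.8 | q = 0.412 | q = 0 |
|---|---|---|---|---|
| 0.9 | 0.9 | 1.00 | 1.00 | 1.00 |
| 0.9 | 0.7 | 1.04 | 1.13 | 1.24 |
| 0.9 | 0.5 | 1.09 | 1.30 | 1.65 |
| 0.7 | 0.9 | 0.95 | 0.87 | 0.80 |

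Over true risks of 20–50 %, the ratio runs from 1.04 to 1.73 when records are the more sensitive source and from 0.79 to 0.96 when they are the less sensitive one.

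**Simpler version, no false positives (Sp = 1).** The true risk cancels:

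- Against all non-caesarean deliveries (q = 0.412): Se(record) / [0.588 × Se(self) + 0.412 × Se(record)]. For 0.9/0.6 this is 0.9/0.7236 = 1.24; for 0.8/0.7 it is 1.08; for 0.9/0.5 it is 1.35.
- Against home deliveries only (q = 0): Se(record)/Se(self). For 0.8/0.7 this is 1.14; for 0.9/0.6 it is 1.5; for 0.9/0.5 it is 1.8.

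Across both versions the spurious ratio spans about 0.8 to 1.8 and includes 1.00.

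**The case against.** A reader might infer that caesarean and antenatal care decide which source is used, and that both will therefore look harmful. The documents do not support this. The source rule for complications gives no order; card first and self-report otherwise is stated only for pregnancy. Vaginal births in a facility also leave records, a card from antenatal care may say nothing about a later home birth, and a hospital record may not be retrievable. The direction of the artefact is unknown. This part of the objection stands.

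Secondly, the endpoints listed at the end of the Background include maternal death but not complications, so mother status in the Data analysis section could mean only dead or alive. On that reading little of the problem remains. However, Study design defines maternal status at delivery with complications inside the same bracket, and complication type is to be documented, so the wider reading follows more naturally.

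Thirdly, all women already answer standardised questionnaires covering childbirth, and the full protocol or forms, not shown here, may rank the sources or hold a source field. That possibility is real. The objection here is to what the article does state: three interchangeable sources, followed by a comparison across exposures linked to them.

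Fourthly, numbers will be small. Taking the sample-size section's 280 women and 20 % pregnant gives 56 pregnancies. With an assumed even split (28 per group) and 30 % risk, the standard error of the log risk ratio is √(2 × 0.7/(28 × 0.3)) = 0.41, so the 95 % interval spans a factor of about 2.2 either way. An artefact of 1.24 would lie well inside that. This limits the practical harm, though longer follow-up adds pregnancies and the bias shifts the whole interval.

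Finally, a reader might conclude that interview answers should replace records altogether. That does not follow. Women delivered in hospital may have been told of diagnoses that others were not, so recall can also differ by exposure, and women who died cannot be interviewed. Nor does any passage say that these particular associations will guide delivery care; antenatal care and caesarean appear as examples in an open list, and the Discussion speaks of policy in general.

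**Conclusion.** The point holds in limited form. As written, the plan can mix data sources differently across the groups it compares, so misclassification of maternal complications can be differential by antenatal care and by caesarean delivery. Nothing in the article standardises the source, records it or allows for it in the analysis.

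The range of about 0.8 to 1.8 illustrates what is possible and does not estimate the bias. It rests wholly on assumed accuracies and on a national home-birth share standing in for the cohort. For antenatal care in particular, the document gives no figure on how many women would have a record of the delivery.

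The point is confined to a secondary outcome and is strongest for the any-complication item. It merits a correction because the remedy is cheap and because, without a source variable, a real association could not be told from an artefact afterwards.

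**What to change.** **Study design (secondary outcomes).** State that every interviewed woman answers the same structured complication questions for each pregnancy, whatever records exist, and that the source or sources used (card, hospital record, interview) are recorded for each pregnancy.

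**Data analysis.** State that comparisons of maternal complications are reported by data source, and add two sensitivity analyses:

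1. the caesarean comparison restricted to facility deliveries with records;
2. the antenatal care and caesarean comparisons using interview answers for all interviewed women.

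State also that associations of antenatal care and caesarean with complications will be interpreted only if they are consistent across these analyses. It would help to say explicitly whether mother status in this section includes complications.

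**Cost.** One extra field on the form, slightly more analysis, and smaller numbers in the restricted comparison. The interview-based analysis cannot include women who died and remains open to recall that differs by exposure, which is why it is proposed as a sensitivity analysis. If data collection is already advanced, recording the source and reporting by it is the minimum.

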### Study setting

#### General setting

Guinea is a coastal West African country with an estimated population of 12 million people [6]. The population is largely rural (65 %) and poor [30]. The Guinean health care system faces many challenges, including chronic shortage of qualified physicians and nurses, and poor clinical infrastructure, particularly in rural and mountainous areas. According to the national action plan for repositioning family planning in Guinea 2014–2018 [20], only 16 % of health professionals (doctors, state midwives and state nurses) work in rural areas where they serve 65 % of the population. Guinea has an estimated lifetime prevalence of obstetric fistula of 0.6 % among women aged 15–49 which ranges regionally from 0.2 to 1.2 % [6], although this figure is likely underestimated. Challenging contextual factors in maternal health include low modern contraceptive prevalence (6 %), concurrent high fertility rate of 5.1, and high maternal mortality (724 deaths per 100,000 live births) [6]. Over the period 2007–2012, the majority of births (54.7 %) were assisted by untrained individuals, and occurred at home (58.8 %) [6]. Since 2012, the Ministry of Health has elaborated a national strategic plan (2012–2016) for the prevention and treatment of fistula [16]. This strategic plan emphasizes the importance of reintegration and support to victims of OF and advocates for more operational and action research that can inform policy.

#### Specific setting

Fistula repair services are available in 4 sites across the country but the study will be conducted with women successfully repaired at the 3 Engenderhealth supported hospitals. From 2007 to 2013, about 3000 OF repairs have been conducted at the 3 Engenderhealth supported sites (Jean Paul II Hospital in Conakry, the Regional Hospital of Labé and the Prefectural Hospital of Kissidougou), where 16 physicians have been trained in obstetric fistula repair, 55 nurses/midwives have been trained in fistula management and 400 − 450 fistula repairs per year have been performed [13].

### Study population

The study population includes all women who underwent successful repair of OF from January 1, 2012 − June 30, 2015 at the 3 above described fistula repair sites.

### Sample size calculation

For the estimation of the incidence rate of the recurrence of fistula, we used the 2-Sided Confidence Intervals for 1 Proportion Confidence Interval Formula [31]. Using the existing data [19] and considering a +/- 2 % margin of error and 95 % confidence interval, we estimate the sample size of the cohort to be 280. We anticipate 20 % loss to follow-up and 10 % refusal rate and accordingly increase the sample size to 364. The same formula provides an estimation of the sample size for the incidence rate of pregnancy [31]. If we estimate the rate of pregnancy to be around 20 % at 24 months’ follow-up among successfully repaired women [20], a sample size of 264 women produces a 2-sided 95 % confidence interval with 10 % precision. Therefore, the sample size of 364 women will be sufficient to describe the objective on pregnancy and its outcomes.

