Despite these improvements, gaps still exist, especially in the long term follow-up of women after successful fistula repair [17]. In fact, data currently available show that delivery leading to fistula usually ends up with a stillbirth [10–12] and that women are relatively young at the time their fistula is repaired [3]. Therefore, when successfully repaired, women return to their community with the desire to resume social and sexual life, and have children [18–20]. However, this return to sexuality exposes repaired woman to pregnancy and childbirth, which increases the risk of recurrence of a previously repaired fistula or the formation of a second, new fistula [18, 19]. Fear of recurrence of fistula is a constant worry for women successfully repaired of OF [21–23] and, given the cost of fistula care and the lower success of repairing [24], these women might need more attention to prevent recurrence of fistula and adverse pregnancy outcomes.

There is no precise estimate of the recurrence of fistula or pregnancy after OF repair. In Ethiopia, Nielsen et al [18] observed 2.63 % re-occurrence of fistula among 38 women in a 21 months’ post-repair median follow up and Browning and Menber [19] recorded 4.26 % in 141 women successfully repaired after 6 months’ follow-up. In Malawi, Wilson et al [20] reported 3.85 % of re-occurrence in 26 women after 9 − 24 months’ follow-up post-repair.

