The same authors found a proportion of pregnancies of respectively 13.16 % [18] and 4.26 % [19] in Ethiopia and 23.10 % in Malawi [20]. Delivery outcomes were poor with only 1 live birth reported in both Ethiopia and Malawi [18, 20]. Heavy work, sexual intercourse, and delivery have been reported to be associated with the recurrence of fistula [25–28]. Because sexuality and desire of children are part of women’s life after successful OF repair [18, 19, 21, 29] and recurrence of fistula and stillbirth are very common complications of delivery post OF repair [18, 20], there is a need for more well powered long term follow-up studies that could fill the existing gap of knowledge. The need to collect long-term follow-up data about fistula recurrence, subsequent pregnancies and their outcomes has already been identified among current research priorities on fistula [17]. Since, there has been no major comprehensive and well powered study initiated in a sub-Saharan African country involving women after OF repair, and for the status of the fistula at discharge is not always specified in the existing studies, we initiated this study with the following objectives:Analyse the incidence rate and risk factors of fistula recurrence up to 48 months follow up.Analyse the incidence rate and factors associated with pregnancy and pregnancy outcomes (maternal and perinatal) up to 48 months’ follow-up;

The endpoints will be recurrence of fistula, pregnancy, abortion or miscarriage, maternal, perinatal and child death at any time from hospital discharge.

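### The ±2 % margin for the primary recurrence estimate rests on a 6-month proportion and names no time point, so it is not a stated precision for cumulative incidence up to 48 months

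*Protocol article*

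**What the plan says.** The Sample size calculation section names the method ("we used the 2-Sided Confidence Intervals for 1 Proportion Confidence Interval Formula") and its inputs ("Using the existing data [19] and considering a +/- 2 % margin of error and 95 % confidence interval"). It concludes: "we estimate the sample size of the cohort to be 280". This is then raised to 364 for 20 % loss to follow-up and 10 % refusal. No time point is attached to the recurrence rate or to its margin. In the same section, the pregnancy calculation does tie its planning rate of about 20 % to 24 months.

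The Background gives the result of source [19]: "recorded 4.26 % in 141 women successfully repaired after 6 months’ follow-up". The first objective is: "Analyse the incidence rate and risk factors of fistula recurrence up to 48 months follow up". Under Study design, the primary outcome is defined so that "recurrence of fistula includes the breakdown of a repaired fistula or the occurrence of a new fistula in study participants". The Data analysis section counts follow-up from hospital discharge, censors women without the event at their last visit, and estimates cumulative incidence.

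**The concern.** The planning rate and the endpoint differ in two ways.

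- **Time.** The rate covers 6 months and the objective runs to 48. Repairs are taken up to June 30, 2015 and follow-up ends on June 30, 2016, so planned follow-up is about 12 months or more for nearly every woman. The planning horizon is shorter than the follow-up of almost the whole cohort.
- **Content.** The endpoint includes new fistulas, and the Background says that later pregnancy and childbirth raise the risk of both breakdown and a new fistula. A term delivery from a conception after repair cannot fall within 6 months of that repair. A 6-month rate therefore cannot contain recurrence after such deliveries.

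At stake is the only quantitative design property claimed for the primary outcome. The Discussion counts the sample size among the study's strengths, and for recurrence that rests on the ±2 %. A reader would take ±2 % as the expected precision of the long-term incidence, which the calculation does not address.

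**Working it through.** **Inputs.** From the sample-size section: margin d = 0.02, two-sided 95 % (z = 1.96), n = 280, inflated to 364. From the Background: 4.26 % of 141 (6 events) at 6 months; 2.63 % of 38 (1 event) at a median of 21 months; 3.85 % of 26 (1 event) at 9 to 24 months.

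**Step 1. The plan's own figure.** The simple (Wald) formula is n = z²p(1−p)/d². With p = 0.0426:

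3.8416 × 0.0426 × 0.9574 / 0.0004 = 391.7, so n = 392, not 280.

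Other usual one-proportion intervals at the same total width need 407 to 454. The Wald formula returns 280 at p of about 3.0 %, a rate the article does not state. This is an arithmetic matter, separate from the time horizon.

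**Step 2. Half-width at the 6-month rate.** h = 1.96 × √(p(1−p)/n) at p = 4.26 %:

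- n = 280: ±2.37 points
- n = 262 (364 × 0.8 × 0.9): ±2.45 points
- n = 364, if nobody were lost: ±2.07 points

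**Step 3. Direction with longer follow-up.** Within one cohort, cumulative incidence cannot fall with time. Below 50 %, p(1−p) rises with p. If the 6-month risk here equals that of [19], the half-width at any later time is at least the Step 2 value.

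**Step 4. Size over an assumed range.** The documents give no 48-month rate, so these rates are assumptions. Follow-up is taken as complete (best case).

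| Cumulative incidence | Half-width, n = 280 | n needed for ±2 |
|---|---|---|
| 4.26 % | ±2.4 | 392 |
| 6 % | ±2.8 | 542 |
| 8 % | ±3.2 | 707 |
| 10 % | ±3.5 | 865 |
| 16 % | ±4.3 | 1290 |

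The 16 % is 1 − (1 − 0.0426)^(24/6), a constant hazard carried from [19] to 24 months.

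Constant-hazard projections of the other two series to 48 months:

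- 1 of 38 at 21 months: 5.9 % (±2.8).
- 1 of 26, all followed 24 months: 7.6 % (±3.1).
- 1 of 26, all followed only 9 months: 18.9 % (±4.6).

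**Step 5. Is the horizon problem only the arithmetic error?** With 392 women, enough for ±2 at 4.26 %, the half-width is about ±2.7 at 8.3 % (constant hazard to 12 months) and ±3.6 at 16 %. Correcting the arithmetic alone would not make ±2 % valid at longer follow-up if the rate rises.

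**Step 6. Censoring.** Women repaired after June 2014 (12 of the 42 repair months) cannot reach 24 months by June 30, 2016. Only those discharged by mid-2012 can reach 48. Kaplan-Meier intervals at those times will be wider than the table shows.

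**The case against.** Four points can fairly be made for the plan.

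- **The visible shortfall is not due to the horizon.** The ±2.4 at 4.26 % comes from the arithmetic. If every recurrence fell within 6 months and none followed a delivery, the horizon would add nothing. This stands: the part due to the horizon starts at zero, and its upper end depends on assumptions. The article does not state that early-only assumption, however, and it sits badly with the childbirth risk in the Background.
- **A steep rise fits poorly with the article's own data.** Constant hazard from [19] gives 1 − 0.9574^3.5 = 14.1 % at 21 months. The exact upper 95 % limit for 1 of 38 is 13.8 %, and the chance of at most one event in 38 at 14.1 % is 0.022 (treating all 38 as followed for the median time). This stands against the 16 % scenario. It stands more strongly against carrying the same hazard to 48 months (29.4 %, ±5.3). A reader might infer that the study needs well over a thousand women or will deliver ±4 to ±5 points; the documents do not support that.
- **No better rate was at hand.** Source [19] is the largest of the three series and has the highest proportion. Either longer series would have given a smaller n. This also stands, so the choice of source is not the fault. Equally, the longer series do not show a low long-term risk: each rests on one event, with exact upper limits of 13.8 % and 19.6 %.
- **Nothing is decided on the margin.** The incidence objective is estimation without a decision rule, and the reported interval will come from the data. This limits the consequence to the design claim.

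**Conclusion.** The point holds as a misstatement of precision. The ±2 % is derived from a 6-month proportion, carries no time point, and is presented for an endpoint that is longer and wider. If the 6-month risk is 4.26 %, the half-width for the study's cumulative incidence is no narrower than ±2.4 points with 280 women. It is about ±2.8 to ±3.5 if the long-term rate is 6 to 10 %, and ±4.3 in an upper scenario of 16 %. All these figures use the Wald formula with complete follow-up and are best cases.

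The documents do not support attributing the whole gap from ±2 % to the horizon, since the first 0.4 points are arithmetic. Nor do they support any single figure for the shortfall, because they do not fix the long-term rate.

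**What to change.** In the Sample size calculation section:

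1. State that the 4.26 % from [19] is a 6-month figure.
2. Withdraw ±2 % as the margin for the study's cumulative incidence.
3. Give the expected half-width of the Kaplan-Meier confidence interval at named times, for example 12 and 24 months, over an assumed range of rates, allowing for the staggered repair dates.
4. Where complete-follow-up figures such as those above are shown, label them as best case, because later repairs are censored before 24 months.
5. Correct the derivation of 280 at the same time, since both changes fall in the same sentences.

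A Kaplan-Meier value at 6 months, for comparison with [19], is optional and can be read from the planned curve.

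The cost is a few sentences and a short calculation. No extra women are needed. The downside is a less favourable stated precision.
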